### Statistical analysis plan

Statistical software package SPSS version 22.0 (SPSS, Inc., Chicago, IL, USA) is used for statistical analysis by a blinded statistician. The following content is a detailed introduction to statistical analysis methods:

#### (1) Data distribution assessment

(a) Normality: Evaluated using the Shapiro–Wilk test (*p* ≥ 0.05 required for normality).

(b) Homogeneity of variance: Assessed via Levene's test (*p* ≥ 0.05 required for equal variances).

#### (2) Between-group comparisons

(a) Parametric approach: For normally distributed data with homogeneous variances, one-way analysis of variance (ANOVA) is performed. If the omnibus test is significant (*p* < 0.05), *post hoc* pairwise comparisons are conducted using Tukey's HSD to control the family-wise error rate (FWER).

(b) Non-parametric approach: For non-normal or heteroscedastic data, the Kruskal–Wallis test is applied, followed by Dunn's test with Bonferroni-adjusted *p*-values (α = 0.017).

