### Randomization and allocation concealment

Participants will be randomly categorized into TNRM-UN, TNRM-TA, or UN groups; the details of the allocation are as follows:

Randomization sequence generation (30): A statistician independent of the research team will generate the randomization sequence using Statistical Package for the Social Sciences (SPSS) version 25.0 (IBM Corp, USA) with a block randomization method. Sequences will be stratified by baseline CVS-FAS score and age to ensure balance between groups. The randomization list is password-protected and stored on a secure server accessed only by an independent statistician.

Allocation concealment protocol (31): Group assignments are sealed in sequentially numbered, opaque envelopes. Each envelope contains a folded card with the group assignment (TNRM-UN, TNRM-TA, or UN). The coordinator, uninvolved in recruitment or outcome assessment, opens envelopes in sequential order only after confirming participant eligibility. Envelopes are stored in a locked cabinet, and an external auditor will access logs weekly.

Preventive Measure of Bias: Participants and outcome assessors are blinded to group assignments. Acupuncturists could not be blinded due to procedural differences, but are instructed not to discuss treatment details. The statistician analyzing outcomes will receive anonymized datasets labeled “Group A/B/C,” and group identities are revealed only after final analysis.

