### Outcome measures

All outcome measurements will be assessed before treatment and after 6 weeks of treatment, and primary outcomes will also be assessed at 12, 24 weeks follow-up.

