### Sample size estimation

PASS V.15.0 software (NCSS, Kaysville, UT, USA) is used for the sample size calculation, and eligible participants are separated into three groups in a 1:1:1 ratio. Owing to the lack of relevant randomized controlled trials (RCTs) and the exploratory nature of this clinical trial, we have to refer to a formula for estimating the sample size of multiple groups of randomized controlled trials: N = [(*Z*_α/2_ + *Z*_β_)σ/δ] (2) (${\text{Q}}_{1}^{-1}$ + ${\text{Q}}_{2}^{-1}$). Based on pre-experiment research data, after 20 patients received TNRM-UN treatment, the average reduction in CVS-FAS was 7.3 points, with a standard deviation of σ = 8.2; the standard deviation (σ = 8.2) in the formula is directly adopted from the pilot study to reflect population variability. Aligned with clinical consensus for vestibular disorders [Jacobson and Newman have supported using a 30%−50% reduction as clinically meaningful in vestibular outcomes in 1990 (40)], we conservatively set δ (δ = 5 points) as 60% of this observed effect. With α = 0.05, 1 – β = 0.9, and the sample number between groups Q1 = Q2 = 0.5, each group required 30 participants. Assuming a 10% dropout rate, 33 participants need to be included in each group; therefore, in total, we included 99 participants. To ensure robustness, we performed sensitivity analyses evaluating: When effect size (δ) variability was 4–6 points and standard deviation (σ) variability was 7.0 – 9.0, the results confirmed that the planned sample size (N = 99) maintained ≥80% statistical power across all plausible scenarios, supporting its adequacy even if assumptions deviated moderately from initial estimates.

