#### (4) Sensitivity analysis

(a) Bonferroni correction: Directly applied to pairwise *t*-tests (adjusted α = 0.017).

(b) Multiple imputation: Missing values are imputed via chained equations (MICE algorithm) with 20 imputed datasets, incorporating baseline covariates and post-dropout outcomes (e.g., adverse events), which will validate results under missing-at-random assumptions. We add psychological status (baseline Hospital Anxiety and Depression Scale [HADS] scores), pain threshold (quantitative sensory testing [QST] for pressure pain tolerance at the trapezius muscle), and sociodemographic factors (age, sex, and education level) as the baseline covariates mentioned here to adjust for reliability of the subjective outcome measures.

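### The between-group test is an unadjusted one-way ANOVA although baseline CVS-FAS and age stratify the randomisation; it is valid but inefficient and, after stratified allocation, conservative

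*Protocol article*

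**What the plan says.** Under Statistical analysis plan, (2) Between-group comparisons, the parametric route is: "For normally distributed data with homogeneous variances, one-way analysis of variance (ANOVA) is performed". If the omnibus test is significant, "pairwise comparisons are conducted using Tukey's HSD to control the family-wise error rate (FWER"). For non-normal or heteroscedastic data, "the Kruskal–Wallis test is applied, followed by Dunn's test with Bonferroni-adjusted" p-values. Neither route has a covariate or a stratum term, and the text does not say whether the analysed variable is the follow-up score or the change from baseline.

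Under Randomization and allocation concealment: "Sequences will be stratified by baseline CVS-FAS score and age to ensure balance between groups". Under Outcome measures: "All outcome measurements will be assessed before treatment and after 6 weeks of treatment". Table 1 likewise schedules CVS-FAS and QBD-SAS at week 0.

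Covariates are named in one place only, (4) Sensitivity analysis, within the multiple-imputation item. Anxiety and depression scores, pain threshold, age, sex and education are added there "as the baseline covariates mentioned here to adjust for reliability of the subjective outcome measures". Baseline CVS-FAS is not in that list.

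**The concern.** The design treats baseline CVS-FAS and age as prognostic enough to stratify on, and the baseline scores are collected in any case. The stated comparison then ignores them.

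Two things follow. First, variation between patients that baseline could explain stays in the error term, so confidence intervals are wider and power is lower than the same data could give. Second, stratification removes part of the chance variation between arms, but an unadjusted standard error is still computed as if that variation were present. The test then rejects less often than its nominal 5% under the null. With about 30 analysable patients per arm, the lost precision matters.

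**Working it through.** **Inputs.** From Sample size estimation: δ = 5 points; pilot SD 8.2 ("the average reduction in CVS-FAS was 7.3 points, with a standard deviation of σ = 8.2"); two-sided α = 0.05; 30 per arm before dropout; stated power 90%. Assumed, because the document does not give it: r, the correlation of baseline with week 6, shown at 0.3, 0.5 and 0.7.

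**The plan's own figure.** The printed formula with Q1 = Q2 = 0.5 gives [(1.960 + 1.282) × 8.2/5]² × 4 = 28.26 × 4 = 113 in total, or 57 per group. The stated 30 is not reproduced. That is a separate point; it matters here only because the starting power is well below 90%.

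**Unadjusted power at 30 per arm.** The noncentrality is 5 / (8.2 × √(2/30)) = 2.36.
- One two-sided 5% t-test (58 df, critical value 2.00): 64%.
- Tukey with three arms (87 df, critical value 2.38): 49%.

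**Adjusted power at 30 per arm.** ANCOVA changes the residual SD. Two readings are needed, each taking 8.2 as the SD of the variable analysed and assuming equal variances at baseline and week 6:
- Change: residual SD = 8.2 × √((1 + r)/2).
- Week-6 score: residual SD = 8.2 × √(1 − r²).

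| r | Change: residual SD | Single test | Tukey | Week-6 score: residual SD | Single test | Tukey |
|---|---|---|---|---|---|---|
| unadjusted | 8.20 | 64% | 49% | 8.20 | 64% | 49% |
| 0.3 | 6.61 | 82% | 71% | 7.82 | 68% | 54% |
| 0.5 | 7.10 | 76% | 63% | 7.10 | 76% | 63% |
| 0.7 | 7.56 | 71% | 57% | 5.86 | 90% | 82% |

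The equivalent gain in sample size is 2/(1 + r) − 1 = 54%, 33%, 18% on change, and 1/(1 − r²) − 1 = 10%, 33%, 96% on the week-6 score. The two readings move in opposite directions with r and meet at r = 0.5. Adjustment gains on both at every r shown.

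**Conservatism, as an illustration only.** Take two arms of 30, with allocation balanced within a median split of a normally distributed baseline. The split accounts for 2/π = 0.64 of the baseline variance. Baseline accounts for (1 − r)/2 of the variance of change and r² of the variance of the week-6 score. The true variance of the arm difference is therefore the nominal one times 1 − 0.64 × that share. At r = 0.5 the share is 0.25 on either reading, the factor is 0.84, and the nominal critical value 2.00 acts like 2.00/√0.84 = 2.18, a true type I error of about 3.3%. Simulation agrees: about 2.5/3.2/4.1% on change and 4.4/3.2/1.9% on the week-6 score for r = 0.3/0.5/0.7, instead of 5%.

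**The case against.** The strongest reply is that an unadjusted ANOVA on randomised arms is valid and that its error here runs in the safe direction. That stands. A reader might infer that the planned test inflates false positives or is wrong in principle; nothing in the document supports that.

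A reader might also infer that any baseline imbalance passes straight into the treatment estimate. That is too strong. CVS-FAS is stratified precisely to limit such imbalance. QBD-SAS is not a stratification factor and is more exposed, but chance imbalance is already allowed for in the test's error rate.

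The size of the gain is uncertain: r is not given and the analysed variable is not named. At r = 0.3 on the week-6 score, power moves only from 64% to 68%. The type I error figures use two arms and an assumed median split, whereas the plan has three arms, an omnibus test, age strata and cut-points that are not stated.

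The covariate sentence under Sensitivity analysis is ambiguous and may be meant as adjustment of the outcome model. Even so, it sits within a sensitivity analysis and does not list baseline CVS-FAS.

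Finally, a journal article may leave detail to a full analysis plan. That does not answer the point: the section presents itself as a detailed account of the methods, and one-way ANOVA is a stated choice.

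**Conclusion.** The point holds as one of efficiency. The planned comparison is valid, but it discards baseline information that the trial collects and stratifies on, and it is conservative as a result. At r = 0.5 the cost is about 12 percentage points of power for a single comparison (64% against 76%) and about 14 under Tukey (49% against 63%). Over r = 0.3 to 0.7 the single-comparison gain runs from about 4 to 26 points, depending on r and on the variable analysed. These figures rest on δ = 5, SD 8.2 for the variable analysed, 30 completers per arm and equal variances at the two visits.

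It would be tempting to read baseline adjustment as a cure for the trial's power. It is not. For a single comparison, 90% is reached only at r of about 0.7 on the week-6 score; every other case shown falls short, and under Tukey all of them do. The sample size needs its own correction.

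**What to change.** Make ANCOVA the primary between-group analysis for each primary score, with arm, the baseline value of that score, and the stratification factors (baseline CVS-FAS and age) as covariates. An equivalent mixed model over weeks 6, 12 and 24 would also serve.

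- Report adjusted pairwise differences with 95% confidence intervals. Use multiplicity-adjusted contrasts (Tukey or Bonferroni on the adjusted means) in place of the unadjusted post hoc tests.
- Keep Kruskal–Wallis with Dunn's test as a sensitivity analysis only, not as an alternative primary route chosen by normality and variance tests.
- Adjust each ultrasound parameter for its own baseline value in the same way.
- State whether the outcome is the score or the change. With the baseline value in the model, the estimated treatment difference is the same either way.

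The cost is a few sentences of analysis text and two or three model terms. No new data, visits or changes to treatment are needed. The change should be fixed before the group labels are revealed, so that nobody can later choose between raw, change and adjusted results.

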The TCM categorizes CV as “cervical paralysis” and “vertigo.” TCM believes that the pathogenesis of CV is mainly due to a deficiency of qi, blood, and the brain medulla. These mechanisms are similar to the theory proposed by modern medicine that CV is caused by an insufficient blood supply to the vertebral arteries. In addition, patients with CV are often accompanied by emotional problems such as restlessness of the heart and mind and depression of liver qi, which makes it difficult to cure the disease. In recent years, TCM has achieved satisfactory results in treating CV. TCM therapies mainly involve Chinese herbal medicine, manual repositioning, acupuncture, massage, cervical traction, and needle-knife therapy (15–20). However, the experimental designs of most clinical trials were not rigorous enough, and it was insufficient for evidence-based medical thinking. These TCM methods (15–20) only have only shown their effectiveness for this disease, and there were shortcomings such as longer treatment course, slower apparent effect, and higher recurrence rate in clinical practice. The author has done a systematic review and meta-analysis (21) that has supported the efficacy of acupuncture for CV. The author has followed [name] cervical vertigo treatment team in clinical practice and experimental research for decades has found that treating CV with qi and blood deficiency is closely related to the regulation of the governor vessel and conception vessel. In recent years, the author has successively established “Dredging governor vessel therapy (22)” and “Dredging governor-regulating conception vessel acupuncture method (23)” to treat CV with deficiency of qi and blood. However, there were still the following shortcomings: (1) Acupuncture therapies brought more pain to patients because of puncturing more acupoints, (2) these therapies did not consider emotional factors, and (3) there were no relevant statistics to long-term efficacy.

To avoid these shortcomings, the efficacy, safety, and cost-effectiveness of TNRM-UN will be compared to those of TNRM-TA or UN through a rigorously designed randomized controlled trial, which will provide a clinical basis for using TNRM-UN for CV with a deficiency of qi and blood.

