(5) While this trial includes a 24-week follow-up period to assess mid-term outcomes, we recognize that this duration may not fully capture the long-term sustainability of therapeutic effects or potential delayed adverse events. To address this gap, we plan to conduct an extended follow-up study (up to 48 weeks) for participants who complete the current trial. This extension will focus on: (a) long-term symptom trajectories: reassessing CVS-FAS and QBD-SAS scores at 36 and 48 weeks to determine durability of symptom relief, (b) delayed adverse effects: monitoring for late-onset complications associated with repeated acupuncture, and (c) patient compliance and behavior: Investigating whether patients adopt supplemental therapies post-trial and their impact on outcomes.

(6) We did not select sham acupuncture as the control arm for two reasons: (a) Acupuncture is very popular in hospitals that recruit participants. Many patients have extensive experience with the sensation of acupuncture, which makes the blinding of participants impractical, even with the design of the sham acupuncture group. (b) The studies revealed that all current sham acupuncture modalities have positive therapeutic effects because they are not absolutely inert (59–61). Then, the therapeutic effect of acupuncture is easily underestimated when compared to sham acupuncture. Therefore, we have not designed a sham acupuncture group as the control. Nevertheless, the therapeutic effect may be influenced by the psychological effects coming from acupuncture, which should be interpreted in the study results.

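### The primary scales are measured at weeks 6, 12 and 24, but the stated between-group tests take one value per participant, so nothing estimates whether the arm difference persists

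*Protocol article*

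**What the plan says.** Outcome measures states that all outcomes are assessed before treatment and after 6 weeks, and that "primary outcomes will also be assessed at 12, 24 weeks follow-up". Table 1 shows both primary scales at weeks 0, 6, 12 and 24, so three measurements follow baseline.

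The Introduction criticises the group's earlier acupuncture methods because "there were no relevant statistics to long-term efficacy", and presents the present trial as designed to avoid such shortcomings.

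The Statistical analysis plan section describes its own account of the methods as detailed. For between-group comparisons it gives: "For normally distributed data with homogeneous variances, one-way analysis of variance (ANOVA) is performed", followed by Tukey's HSD if the omnibus test is significant. Otherwise it gives Kruskal-Wallis, followed by Dunn's test at a Bonferroni level of 0.017. Within-group comparisons are paired pre-post tests. The sensitivity analyses are Bonferroni-adjusted pairwise t-tests and multiple imputation. None of these contains a visit factor or an arm-by-visit contrast.

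**The concern.** One-way ANOVA and Kruskal-Wallis accept a single value per participant. With three post-baseline visits, the plan as written most naturally yields separate between-arm tests at weeks 6, 12 and 24, on scores or change scores. Each such test can be valid for its own visit. None says whether the arm difference at week 24 is smaller than, equal to or larger than that at week 6.

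The risk lies in interpretation. If week 6 is significant and week 24 is not, a reader will tend to conclude that the effect faded; if both are significant, that it lasted. Neither follows, because a difference in significance between two visits is not a test of change. In a trial with moderate power, discordant visits are common even when the true effect is constant. The trial's contribution on later efficacy would then rest on no estimate suited to it.

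**Working it through.** **Inputs from Sample size estimation.** Two-sided α and power: "With α = 0.05, 1 – β = 0.9". SD: "the average reduction in CVS-FAS was 7.3 points, with a standard deviation of σ = 8.2". True difference: δ = 5. Per arm: 30 evaluable, 33 enrolled. Between-visit correlation ρ is not stated, so it is assumed and varied from 0.3 to 0.9.

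**Step 1: the plan's own figure.** Reading the printed 2 as an exponent, the formula is N = [(Z_α/2 + Z_β)σ/δ]² × (1/Q1 + 1/Q2).
- Core term: (1.96 + 1.2816) × 8.2/5 = 5.316; squared, 28.3.
- With Q1 = Q2 = 0.5 the last factor is 2 + 2 = 4, so N = 113 for two groups, or 57 per group.

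The stated 30 per group is not reproduced. The core term without the last factor (28.3, rounded up to 29) comes close to it.

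**Step 2: power for one pairwise comparison at one visit.** The SE of the difference is 8.2 × √(2/n).
- n = 30: SE 2.117, standardised effect 5/2.117 = 2.36.
- n = 33: SE 2.019, standardised effect 2.48.
- Unadjusted (critical value 1.96): power 0.66 and 0.70.
- Tukey, three groups (critical value about 2.38): power 0.49 and about 0.53-0.54.

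**Step 3: discordant visits under a constant effect.** The quantity is P(not significant at week 24 | significant at week 6) = 1 − P(both)/P(week 6). The stated rule (omnibus F at 0.05, then Tukey) was simulated with 40,000 trials per setting and both controls worse by 5:

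| ρ | n = 30 | n = 33 |
|---|---|---|
| 0.3 | 0.42 | 0.37 |
| 0.5 | 0.35 | 0.32 |
| 0.7 | 0.27 | 0.24 |
| 0.8 | 0.21 | 0.19 |
| 0.9 | 0.15 | 0.14 |

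A bivariate normal calculation for the Tukey comparison agrees within about 0.01. At n = 30 and ρ = 0.5, P(both) = 0.324 and P(week 6) = 0.491, giving 1 − 0.324/0.491 = 0.34.

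**Step 4: how much is due to low power.** With a single unadjusted test at n = 30 the share is 0.23 at ρ = 0.5 and 0.18 at ρ = 0.7. With 57 per group, where the unadjusted test does have 90% power, it is 0.07 and 0.06.

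**Step 5: what a direct contrast can deliver.** The change in arm difference from week 6 to week 24 has SE = σ√[4(1 − ρ)/n]. At ρ = 0.6 and n = 30 this is 8.2 × √(1.6/30) = 1.89. With a t critical value of about 2.00 the 95% CI is ±3.8 points. If a 5-point effect halved, the standardised change would be 2.5/1.89 = 1.32, so power is about 26%. Under a constant effect the contrast rejects in about 5% of trials, as any valid 5% test must.

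**The case against.** Four objections have force.

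**Durability is not a formal objective.** A reader might cite the phrase "to determine durability of symptom relief" in Limitations as showing that it is. That sentence concerns a planned extension with assessments at weeks 36 and 48; the same item calls the 24-week data mid-term. It does not support the point. What remains is the Introduction's complaint about missing long-term data, and a between-arm comparison at week 24 partly answers that.

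**The article sets no rule of comparing p-values between visits.** A reader might infer that it will judge persistence this way; nothing says so. The percentages are the error rate of that reading if it is made.

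**The population at each visit is not described.** A reader might infer that each visit's test uses only those who attended, so that weeks 6 and 24 compare different people. The article does not say this. It plans multiple imputation, though only as a sensitivity analysis.

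**The figure is not fixed by the document.** It depends on an unstated correlation, and it is high largely because 30 to 33 per arm gives about 50% pairwise power under Tukey. Nor should it be set against the 5% of the direct contrast as like for like: the latter is a type I error rate by construction, and that contrast has little power to detect fading.

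It can also be said that a longitudinal contrast is often left to a separate analysis plan. This carries less weight here, because the article presents its methods as detailed and names specific tests that do not use the repeated structure of its own primary outcomes.

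**Conclusion.** The point holds in a limited form. The stated between-group methods are single-time-point tests applied to outcomes measured three times after baseline, and no stated analysis estimates whether the arm difference persists from week 6 to week 24. That separate tests at each visit are meant is an inference, though the natural one.

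If persistence were read from the pattern of significance, about 24-35% of trials significant at week 6 would be non-significant at week 24 despite a constant effect. This assumes a difference of 5, SD 8.2 (the pilot SD of the reduction) at each visit, 30 to 33 per arm, the Tukey rule and correlations of 0.5-0.7. For correlations of 0.3-0.9 the span is about 14-42%. Much of it comes from low power rather than from the choice of test.

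The week 6 comparison is not invalidated by this; what is affected is the support for any statement about later efficacy.

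**What to change.** For each primary scale, replace the separate tests by one mixed model for repeated measures:
- arm, visit and arm × visit as fixed effects, with the baseline score as covariate and unstructured covariance;
- all observed post-baseline visits (weeks 6, 12 and 24) of all randomised participants;
- arm differences at each visit taken from this model;
- multiplicity control kept over the three pairwise comparisons, for example the Bonferroni level of 0.017 already in the plan, since removing the ANOVA would also remove Tukey's protection;
- the change in arm difference from week 6 to week 24 reported with its 95% CI.

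Add two statements: that persistence is not judged by comparing p-values between visits, and that the interval for the change will be wide (the ±3.8 points above), so a non-significant change is not proof of durability.

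The model alone does not solve the problem; the contrast has to be named. The cost is a revised analysis paragraph and a few lines of the SPSS MIXED procedure. No new data or visits are needed.

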**Methods:**

This was a single-center, assessor-, and analyst-blinded, prospective randomized controlled trial that involved treatment for 6 weeks and follow-up for 24 weeks. Ninety-nine patients with CV deficiency of qi and blood are randomly allocated to three groups in a 1:1:1 ratio. The patients in the observation group will receive three-needle of regulating the mind combined with umbilical needle (TNRM-UN) therapy. In contrast, the patients in the control-1 group will receive three-needle of regulating the mind combined with traditional acupuncture (TNRM-TA), and the patients in the control-2 group will receive only umbilical needle (UN) therapy. Primary outcomes include Cervical Vertigo Symptom and Functional Assessment Scale (CVS-FAS) score and qi and Blood Deficiency Symptoms Assessment Scale (QBD-SAS) score. The secondary outcomes are hemodynamic changes in the bilateral vertebral arteries, including diameter value (DV), peak systolic velocity (PSV), end-diastolic velocity (EDV), pulsatility index (PI), and resistance index (RI). All outcome measurements will be evaluated before and after 6 weeks of treatment. Primary outcomes will be evaluated at 12 and 24 weeks of follow-up. Adverse events (AEs) were evaluated during treatment and follow-up periods.

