The innovations in the intervention approach of this study are explained as follows: Regarding the three-needle method of regulating the mind, its theoretical basis is the meridian system theory of TCM, the stimulated meridian qi is acquired meridian qi, the acupuncture site is in the brain, and the acupuncture points are located in the governor vessel. Regarding umbilical needle therapy, its theoretical basis is Yi Jing theory, the stimulated meridian qi is innate, the acupuncture site is in the umbilical region, and the acupuncture point is located in the conception vessel. Umbilical needle therapy breaks through the 1,000 of years confinement of “Shen que forbidding needles” and paves the way for the precedent of “one point curing hundreds of diseases.” This study is the first attempt to combine the two methods in treating CV. This method combines the theory of TCM and Yi Jing, the combination of the human brain and umbilical cord, the combination of the governor vessel and conception vessel, and the combination of the innate and acquired meridians. This method has the advantages of few acupuncture points, simple operation, and less pain. While it appears to be simple, it contains a great deal of theoretical basis and information, and fully embodies the holistic view of TCM and the principle of “the way is simple.”

The innovations in the control setting of this study are explained as follows: (1) The three-needle regulating the mind combined with the traditional acupuncture group was compared to the three-needle regulating the mind combined with the umbilical needle group. Both groups received initial treatment with three needles to regulate the mind for mental relaxation, and there was only a difference in the single factor of “traditional acupuncture” or “umbilical needle.” This study aimed to confirm the superiority of the umbilical needle compared with traditional acupuncture as a control. (2) The three-needle regulating the mind combined with the umbilical needle group was compared with the umbilical needle-only group. Both groups received treatment with an umbilical needle, and there was only a difference in the single factor of whether a three-needle regulating the mind was used. We propose to confirm the importance of using a three-needle to regulate the mind in CV.

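### Error is controlled only within one scale at one visit: two primary scales at three visits make six primary tests, each at 5%, with no primary visit, ranking or success rule

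*Protocol article*

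**What the plan says.** The Abstract (Methods) states: "Primary outcomes include Cervical Vertigo Symptom and Functional Assessment Scale (CVS-FAS) score and qi and Blood Deficiency Symptoms Assessment Scale (QBD-SAS) score". The section on primary outcome measures lists the same two scales. Both are measured after 6 weeks of treatment, and under Outcome measures "primary outcomes will also be assessed at 12, 24 weeks follow-up". Table 1 shows the same schedule.

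The Statistical analysis plan, part (2), begins each parametric comparison with a one-way ANOVA. It continues "If the omnibus test is significant (*p* < 0.05") with pairwise comparisons by Tukey's "HSD to control the family-wise error rate (FWER"). The non-parametric route is Kruskal–Wallis followed by "Dunn's test with Bonferroni-adjusted *p*-values (α = 0.017"). The sensitivity analysis in part (4) applies the same 0.017 to pairwise t-tests.

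The sample size section uses CVS-FAS alone, "With α = 0.05, 1 – β = 0.9", and names no visit. No section designates a primary visit, ranks the two scales, or says whether success needs one scale or both.

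**The concern.** The error control described protects the three pairwise comparisons that follow one omnibus test. The primary family as the protocol defines it is wider, because two scales at three post-baseline visits give six omnibus tests. Nothing is adjusted across them, and no order or designated visit says which result decides the trial.

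That leaves the primary conclusion open until the data are seen. An effect on either scale, at any of three visits, could be reported as a positive primary outcome at the nominal 5% level. A null result on CVS-FAS at the end of treatment could be passed over in favour of QBD-SAS at week 24 without departing from the written plan.

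**Working it through.** **Inputs from the protocol.** Two primary scales (Abstract; primary outcome measures). Visits at weeks 6, 12 and 24 (Table 1; Outcome measures). Omnibus level 0.05, then Tukey, or Dunn at 0.017 (Statistical analysis plan, part 2). 30 evaluable participants per group (Sample size estimation). The stated aim is superiority of TNRM-UN over its controls (Strengths of the study).

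**The plan's own figure.** 0.05 / 3 = 0.0167, printed as 0.017. It reproduces, and the divisor shows what is covered: three group pairs. There is no factor for scales or visits.

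**Number of primary tests.** 2 scales × 3 visits = 6 omnibus tests at 0.05. The reassessments at 36 and 48 weeks in the Limitations belong to a planned extension and are not counted.

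**Upper limit, independent tests.** 1 − (1 − 0.05)^6 = 1 − 0.735 = 26.5%.

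**Correlated tests.** Scores on the same patients are correlated, but the protocol gives no correlations, so they are assumed. Simulation settings: all arms equal, normal data, 30 per arm at every visit, ANOVA at 0.05 followed by Tukey. Each setting had 20,000 trials (Monte Carlo error about 0.3 points). The correlation between different scales at different visits is taken as the product of the two values shown.

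| Correlation between visits / between scales | At least one of six omnibus tests significant | Same, with at least one significant Tukey pair | TNRM-UN declared better than at least one control |
|---|---|---|---|
| 0 / 0 | 26.9% | 24.5% | 9.5% |
| 0.5 / 0.5 | 22.1% | 20.0% | 7.5% |
| 0.7 / 0.5 | 19.2% | 17.6% | 6.6% |
| 0.8 / 0.6 | 17.5% | 16.0% | 6.0% |
| 0.8 / 0.8 | 15.5% | 14.2% | 5.5% |
| 0.9 / 0.9 | 12.1% | 11.2% | 4.2% |

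**Reference: one scale at one visit.** In a separate simulation of a single test under the same conditions, the omnibus test is significant in 5.0% of trials. TNRM-UN is declared better than at least one control in 1.6%. As a check, six independent tests give 1 − (1 − 0.016)^6 ≈ 9%, in line with the first row.

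**Inflation for the stated aim.** 4.2 / 1.6 ≈ 2.6 times at the highest correlations and 9.5 / 1.6 ≈ 5.9 times under independence. TNRM-UN falsely beating both controls in the same test stays below 1% at every setting.

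**Effect of the fix.** One scale at one visit returns the omnibus error to 5%. Two scales at one visit, either sufficing, give 1 − 0.95² = 9.75% if independent and about 7–10% over the correlations above. At 0.025 each the sum is at most 5%. If both must succeed, no split is needed. Keeping all six tests as primary would need 0.05 / 6 = 0.0083 each.

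**The case against.** **The Tukey sentence is true.** It speaks of pairwise comparisons after an omnibus test, and within that family Tukey does control the error. A reader might infer that the protocol makes a false study-wide claim. It does not: it never claims control across scales or visits. The fault is that the primary hypothesis is left undefined.

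**A reader might infer a false-success rate of up to 27% for TNRM-UN.** The calculation does not support that. The 12–27% counts any significant omnibus test, including differences between the two controls, results with TNRM-UN worse, and omnibus results with no significant pair. For TNRM-UN favoured over at least one control the figure is 4–10%. The top of each range needs independent tests, which is implausible for repeated scores on the same patients.

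**A reader might also infer that Tukey is the wrong method.** The Strengths section sets out two contrasts, TNRM-UN against each control, and Tukey also covers the third pair. For the planning values (difference 5, SD 8.2, 30 per group), power is about 49% with Tukey and 55% with Dunnett on two contrasts. Both methods are valid, so this is a preference and not an error.

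**The trial is called exploratory, and detail may sit in a separate analysis plan.** The sample size section does use that word, which softens the point. But the Strengths section says "This study aimed to confirm the superiority of the umbilical needle compared with traditional acupuncture as a control", which is confirmatory language. An adjustment across endpoints could reasonably be left to a separate plan. Here, however, the protocol itself makes two scales primary at three visits and sets every test at 0.05, and a primary visit normally belongs in the protocol.

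**Conclusion.** The concern holds in this form: the planned error control reaches only the three group pairs within one scale at one visit, while the protocol leaves six primary omnibus tests at 0.05 with no primary visit, ranking or success rule. With all arms equal, the chance of at least one false significant omnibus result is about 12–27%. For a false finding that TNRM-UN beats at least one control it is about 4–10%, against about 1.6% for a single test.

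Both ranges rest on assumed correlations of 0 to 0.9, on 30 evaluable participants per arm at each visit, and on the ANOVA and Tukey route. The Kruskal–Wallis and Dunn route was not simulated, but its 0.017 has the same scope. The number of tests and the missing primary visit do not depend on these assumptions.

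**What to change.** Name one primary scale and one primary visit. CVS-FAS is the natural scale because the sample size is built on it. Week 6, the end of treatment, is a reasonable visit, but that is a choice for the sponsor, since the sample size section states none. Test it between groups at 5% with the pairwise control already planned. Test QBD-SAS and the later visits as secondary in a fixed order, and state which result opens each next step.

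Alternatively, keep both scales as primary at one named visit and choose one rule:
- Both scales must succeed, each tested at 5%.
- Either scale suffices, each tested at 0.025, with the pairwise step tightened to match (for Dunn, 0.025 / 3 = 0.0083).

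The cost is a change of wording in the protocol and any analysis plan, plus a registry update, made before group results are seen. The downside is small: the other scale or visits lose primary status, or alpha is split. Requiring both scales to succeed also lowers power. Restricting the tests to the two contrasts in the Strengths section, with Dunnett or Holm, is optional and not needed to correct the error.
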